### **Non-serious Adverse Event**

- Non-serious Adverse Events (AE) are to be provided to BMS in aggregate via interim or final study reports as specified in the agreement or, if a regulatory requirement [*i.e.* IND US trial] as part of an annual reporting requirement.
- Non-serious AE information should also be collected from following the subject's written consent to participate in the study.

### **Non-serious Adverse Event Collection and Reporting**

The collection of non-serious AE information should begin following the subject's written consent to participate in the study. All non-serious adverse events (not only those deemed to be treatment-related) should be collected continuously during the treatment period and for a minimum of 100 days following the last dose of study treatment.

Non-serious AEs should be followed to resolution or stabilization, or reported as SAEs if they become serious. Follow-up is also required for non-serious AEs that cause interruption or discontinuation of study drug and for those present at the end of study treatment as appropriate.

### Laboratory Test Abnormalities

All laboratory test results captured as part of the study should be recorded following institutional procedures. Test results that constitute SAEs should be documented and reported to BMS as such.

The following laboratory abnormalities should be documented and reported appropriately:

- any laboratory test result that is clinically significant or meets the definition of an SAE
- any laboratory abnormality that required the participant to have study drug discontinued or interrupted
- any laboratory abnormality that required the subject to receive specific corrective therapy.

It is expected that wherever possible, the clinical rather than laboratory term would be used by the reporting investigator (*i.e.* anemia versus low hemoglobin value).

### Other Safety Considerations

Any significant worsening noted during interim or final physical examinations, electrocardiograms, X-rays, and any other potential safety assessments, whether or not these procedures are required by the protocol, should also be recorded as a non-serious or serious AE, as appropriate, and reported accordingly.

A special section is designated to adverse events in the eCRF. The following details must thereby be entered:

- Type of adverse event
- Start (date and time)
- End (date and time)
- Severity (Grad 1-5)
- Serious (no / yes)
- Unexpected (no / yes)
- Outcome (resolved, resolving, not resolved, resolved with sequelae, unknown, fatal)
- Relation to study drug (Related / Not related)

Adverse events are to be documented in the eCRF in accordance with the above-mentioned criteria.

## 9.6.1 Reporting procedures for SUSAR

It must be remembered that the regulatory authorities, and the Institutional Review Board / Independent Ethics Committee (IRB / IEC) must be informed about all SUSAR. Such reports shall be made by the sponsor and should contain at least the following details:

- Patient number (study code/screening number)
- Patient: age in years, sex
- Name of Investigator and investigating site
- Period of administration
- The suspected investigational medical product (IMP)

[figure not shown]

- The adverse event assessed as serious and unexpected, and for which there is a **suspected** causal relationship to the IMP
- Concomitant disease and medication
- Short description of the event:
  - Description
  - Onset and if applicable, end
  - Therapeutic intervention
  - Causal relationship
  - Seriousness criteria or reportable reason

Electronic reporting should be the expected method for reporting of SUSARs to the competent authority. In that case, the format and content as defined by the regulatory requirements should be adhered to. The latest version of MedDRA should be applied. Lower level terms (LLT) should be used.

### 9.6.2 Development safety update report

A Development Safety Update Report (DSUR) will be provided by the Sponsor annually.

This report will also be presented annually to the Independent Ethics (IEC) and to the competent authorities by the sponsor, as well as to BMS.

[figure not shown]

## 10 FOLLOW-UP

### 10.1 Follow-up of study participants including follow-up of adverse events

Study specific follow-up for safety, tolerability and feasibility will end after EOS. Nevertheless, patients will undergo standard oncologic follow-up, including recurrence-free survival (RFS) and overall survival (OS), according to the latest ESMO guidelines for local/locoregional rectal cancer [3].

### 10.2 Treatment after end of study

There will be no study related treatment after end of study.

[figure not shown]

## 11 STATISTICAL METHODOLOGY AND ANALYSIS

### 11.1 Analysis sets

#### Treatment set

This analysis set includes all subjects who were randomized to the treatment arm and received neoadjuvant CRT with sequential Ipilimumab and Nivolumab and did not violate the protocol in a way that might affect the evaluation of the effect of the study drugs on the primary objective.

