#### Replacement policy

Patients who discontinue the clinical trial before receiving the first cycle of treatment will be replaced. All other drop-outs will be included in the sample size.

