#### Control set

This analysis set includes all subjects who were randomized to the control arm and received neoadjuvant CRT and did not violate the protocol in a way that might affect the evaluation of the effect of the study drugs on the primary objective.

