#### 11.4.3 Secondary endpoint analysis

Statistical analysis of secondary objectives, especially between control and treatment arm will be performed according the nature of the outcome parameter. Nominal and dichotomous, outcomes will be compared by Chi-squared or Fisher's exact tests, continuous variables will be compared by T-tests (after  $\log_2$  transformation) or by Mann-Whitney-U tests and censored survival outcomes by Cox-regression analysis. Potential confounders will be considered in corresponding statistical models. Multiple testing will be corrected for by the Holm's Step-Down method or by the false discovery rate (FDR) method after Benjamini-Hochberg (especially omics data) [42]. Adjusted p-values (q-values) below 0.05 will be considered as statistically significant.

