#### 11.4.4 Safety and tolerability endpoints

The safety analysis will be performed in all participants who have received at least 1 dose of study treatment. Descriptive statistics of safety will be presented using latest NCI CTCAE by treatment arm. Adverse events, treatment-related AEs, SAEs and treatment-related SAEs will be tabulated using worst grade per latest NCI CTCAE criteria by system organ class and preferred term. On-study lab parameters including hematology, chemistry including liver function and renal function will be summarized using worst grade per latest NCI CTCAE criteria.

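### Section 11.1 defines only per-protocol sets with unequal entry rules and 11.4.3 names no set, so randomisation does not protect the between-arm comparison of response

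*Protocol*

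**What the plan says.** Section 11.1 defines one set per arm. The treatment set contains patients "randomized to the treatment arm and received neoadjuvant CRT with sequential Ipilimumab and Nivolumab and did not violate the protocol". By the section's own qualification, a violation counts only if it occurred "in a way that might affect the evaluation of the effect of the study drugs on the primary objective". The control set contains patients "randomized to the control arm and received neoadjuvant CRT and did not violate the protocol", with the same qualification. That qualification is tied to the primary objective, which is safety.

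Section 11.4.3 opens with "Statistical analysis of secondary objectives, especially between control and treatment arm will be performed according the nature of the outcome parameter". It then lists tests by type of variable and names no analysis set. The secondary objectives in section 6.2 include mrTRG, pathological TRG and tumour stage.

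One further population appears, in section 11.4.4, for safety only: "The safety analysis will be performed in all participants who have received at least 1 dose of study treatment". The replacement policy in section 7.1.6 adds: "Patients who discontinue the clinical trial before receiving the first cycle of treatment will be replaced". On later losses, the same policy states: "All other drop-outs will be included in the sample size".

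**The concern.** Randomisation makes two arms comparable as long as patients are analysed as assigned. Here a treatment-arm patient must meet a condition after randomisation, receipt of both immunotherapy drugs, that a control patient does not face. A treatment-arm patient who completes CRT but stops before the immunotherapy condition is met can leave the set. A control patient with the same clinical course stays. Relevant violations must also be judged by people who know the allocation, because the trial is open-label (section 8.5), and section 8.6 already expects a major gain in pathological response in the treatment arm.

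At stake is how a difference in regression grade or stage between the arms can be read. If the sets differ in who was removed, part of that difference may be selection and not drug effect. The trial randomises 50 and 30 patients, and this comparison is where randomisation would be most useful for judging activity.

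**Working it through.** **1. The entry rules side by side**

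| Condition | Treatment set | Control set |
|---|---|---|
| Randomised to the arm | required | required |
| Received CRT | required | required |
| Received ipilimumab, then nivolumab | required | no counterpart |
| No violation relevant to the primary objective | required | required |

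The third row is the asymmetry. The fourth is worded alike in both arms but is framed around safety, so neither set was built for response. Sections 11.1 and 11.4 contain no all-randomised set.

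**2. How strict the third row is**

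Section 8.2.3 schedules ipilimumab on day 7 and nivolumab every two weeks from day 14 to day 42, three cycles in all. The protocol does not say what *received* means.
- If it means at least one dose of each drug, a patient fails by stopping before day 14.
- If it means the whole sequence, a patient can fail at any point up to day 42.

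On either reading the treatment-arm rule is stricter than the control rule. The share of patients affected differs between the readings.

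**3. Possible size**

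The protocol gives no response rate, no responder cut-off and no expected rate of immunotherapy discontinuation. Its only power figure, 49 patients for surgical complications of 46% against 23% (section 11.2), has no bearing on this point. The inputs below are therefore assumptions:
- *q*, true response in the whole arm, the same in both arms (no drug effect): 20%
- *d*, share of the treatment arm excluded: 10% or 20%, leaving 50 × 0.90 = 45 or 50 × 0.80 = 40 patients
- *r*, response among those excluded: 0% to 40%
- no exclusions in the control arm

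Observed treatment-set rate = (*q* − *d* × *r*) / (1 − *d*).

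| *d* | *r* | Calculation | Observed | Shift (points) |
|---|---|---|---|---|
| 10% | 0% | 0.20 / 0.90 | 22.2% | +2.2 |
| 10% | 10% | 0.19 / 0.90 | 21.1% | +1.1 |
| 10% | 20% | 0.18 / 0.90 | 20.0% | 0 |
| 10% | 40% | 0.16 / 0.90 | 17.8% | −2.2 |
| 20% | 0% | 0.20 / 0.80 | 25.0% | +5.0 |
| 20% | 10% | 0.18 / 0.80 | 22.5% | +2.5 |
| 20% | 20% | 0.16 / 0.80 | 20.0% | 0 |
| 20% | 40% | 0.12 / 0.80 | 15.0% | −5.0 |

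The sign depends only on whether *r* is below or above *q*. More extreme assumptions give more: *q* = 30%, *d* = 30%, *r* = 0% gives 0.30 / 0.70 = 42.9%, a shift of +12.9 points.

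Exclusions from the control set would offset some of this. If 10% of controls were also removed and all were non-responders, the control rate would be 22.2%. The largest gap in the table would then shrink from 5.0 to 25.0 − 22.2 = 2.8 points.

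**The case against.** The strongest reply is that the protocol never says the 11.1 sets apply to response. Their violation clause concerns safety, 11.4.3 is silent, 11.4.1 imputes missing secondary data where appropriate, and later drop-outs count in the sample size. The last two sit awkwardly with dropping such patients. This is fair: use of the 11.1 sets for response is an inference. It is still the natural one, because no other set exists for that purpose. Imputation fills missing values; it does not bring back patients whom a set definition has removed. Nor is this detail simply deferred to a separate SAP, since the protocol fixes the sets itself.

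A reader might infer that the comparison is selected in favour of immunotherapy. The protocol does not show that. It would require excluded patients to respond worse than those kept, and the withdrawal reasons in section 7.1.6 (own request, toxicity, pregnancy, non-adherence, investigator judgement, study termination) do not establish it. Section 8.2.12 reports preliminary results that immunosuppression after the start of nivolumab does not appear to prevent response. A bias towards treatment is plausible if early stoppers respond worse, but no more than that.

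A reader might also infer that a survival comparison is compromised. Cox regression is listed in 11.4.3, but section 6.2 names no survival endpoint and section 10.1 leaves recurrence-free and overall survival to routine follow-up.

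Finally, the shift is small against sampling error. At 20% in both arms the standard error of the difference is √(0.16/50 + 0.16/30) = 0.092, or about ±18 points at 95%. That limits the practical weight of this secondary, unpowered comparison. It does not justify adding an avoidable bias to it.

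**Conclusion.** The point holds as a defect in the analysis-set definitions. Both sets are per-protocol, entry is stricter in the treatment arm because of a condition met after randomisation, *received* is undefined, and no all-randomised set is available for the between-arm tests in 11.4.3. Read naturally, the plan compares mrTRG and pathological response without the protection of randomisation.

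The bias is possible, and its sign is not determined by the protocol. With 20% true response in both arms, 10–20% of the treatment arm excluded and no control exclusions, the treatment-arm rate moves by 0 to +5 points if excluded patients respond no better than the arm average, and moves down if they respond better. These figures rest wholly on the stated assumptions. The point concerns the response objectives only; the safety verdict is not affected.

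**What to change.** Add to sections 11.1 and 11.4.3:

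- The response objectives (mrTRG, TRG, ypT and ypN) are compared in all randomised patients by assigned arm, including patients who were later replaced.
- A missing specimen or MRI result is handled by one stated rule, applied identically in both arms and consistent with the imputation in 11.4.1, with a sensitivity analysis. Counting every patient without a specimen as a non-responder is not advised as the main rule. It would need a responder cut-off that the protocol lacks, and it would conflict with 11.4.1.
- The present treatment and control sets are kept as supportive analyses, with *received* defined.

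The cost is wording in the analysis sections. No treatment, visit or sample size changes, and no survival endpoint is added. Section 12.1.1 already requires an eCRF for every enrolled patient whether or not study drug was started, so the denominators can be obtained. There are two modest downsides. The effect is diluted somewhat by patients who did not receive the drugs. Some response data will also be missing, because under section 7.1.6 withdrawn patients may decline further assessments and recording.

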### 7.1.6 Withdrawal and replacement of subjects

#### Criteria for withdrawal

Subjects may prematurely discontinue from the study at any time. Premature discontinuation from the study means that the subject did not undergo an end of study (EOS) examination as planned per protocol.

Subjects must be withdrawn under the following circumstances:

- at their own request
- if the Investigator feels it would not be in the best interest of the subject to continue
- if the subject violates conditions laid out in the consent form / information sheet or disregards instructions by the study personal
- in case of unacceptable toxicity
- in case of pregnancy of the subject
- if the entire study is terminated for medical or ethical reasons

In all cases, the reason why subjects are withdrawn must be recorded in detail in the eCRF and in the subject's medical records. Should the study be discontinued prematurely, all study materials (completed, partially completed and empty eCRFs) will be retained.

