#### Follow-up of patients withdrawn from the study

In case of premature discontinuation after study drug intake, the investigations scheduled for the EOS visit will be performed 28 days after study drug discontinuation. The subjects will be advised that participation in these investigations is voluntary. Furthermore, they may request that from the time point of withdrawal no more data will be recorded and that all biological samples collected in the course of the study will be destroyed.

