### 8.2.6 Study drug premature permanent discontinuation

#### **Study drug premature permanent discontinuation due to an adverse event**

If the reason for premature permanent discontinuation of study treatment is due to a specification in the drug specific SmPC, the patient should have a “Premature End of Study (EOS)” visit with all the assessments performed before the study drug discontinuation, whenever possible.

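### Patients who stop immunotherapy for toxicity have no consistent route into the primary safety count, and a border fixed at n=50 turns each gap towards a verdict of safe

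*Protocol*

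**What the plan says.** **Leaving the study.** Section 7.1.6 lists the circumstances in which a subject must be withdrawn, among them "in case of unacceptable toxicity". It defines the consequence: "Premature discontinuation from the study means that the subject did not undergo an end of study (EOS) examination as planned per protocol". After a premature stop, "the investigations scheduled for the EOS visit will be performed 28 days after study drug discontinuation", and attendance is voluntary. Section 8.2.6 adds that, where the drug is permanently stopped under its product information, "the patient should have a “Premature End of Study (EOS)” visit with all the assessments performed before the study drug discontinuation, whenever possible". Section 10.1 ends study-specific safety follow-up after EOS.

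**Event collection.** Section 9.6 collects non-serious adverse events "for a minimum of 100 days following the last dose of study treatment", and serious events for 100 days after dosing stops.

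**Who is counted.** Section 11.1 defines a treatment set of randomised patients who "received neoadjuvant CRT with sequential Ipilimumab and Nivolumab and did not violate the protocol in a way that might affect the evaluation". The replacement policy in 7.1.6 says of anyone lost after the first cycle: "All other drop-outs will be included in the sample size". Section 11.4.2 describes the treatment arm as 50 patients. Section 11.4.4 states: "The safety analysis will be performed in all participants who have received at least 1 dose of study treatment".

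**The decision.** Section 11.4.1 excludes a patient with missing data on an event from the evaluation of that event. The synopsis and section 11.4.2 compare the number of cases of each complication with an upper border calculated for 50 patients (Table 2). A count above the border means unsafe.

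**The concern.** The primary objective is safety, and its decision rule counts complications of surgery. Toxicity from the study drugs is itself the reason some patients leave the study before surgery. If their outcomes are not collected, the loss depends on the property under test and occurs only in the treatment arm.

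The form of the rule makes this worse. It compares a raw count, not a proportion, with a limit that does not shrink when fewer patients are evaluated. A patient without an observed outcome can add nothing to the count, whether excluded from the set or kept among the 50 with no event recorded. At stake is whether the trial would detect the doubling of surgical complications that section 11.2 says it can exclude.

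**Working it through.** **1. The plan's own figures.** Table 2, 22.5% row (the row nearest the published 23%): 0.225 × 50 = 11.25, rounded to 11 cases. The exact 95% upper limit for 11 of 50 is 17.98 cases, rounded to the printed 18. At exactly 23%, 11.5 rounds to 12 and the border is 19.

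The 49 patients in section 11.2 reproduce best as a one-sided comparison (α = 0.05) with the 128 historical patients in Table 1; the protocol does not state the method. The pooled rate is (49 × 0.46 + 128 × 0.23)/177 = 0.294. Power = Φ{[0.23 − 1.645 × √(0.294 × 0.706 × (1/49 + 1/128))] / √(0.46 × 0.54/49 + 0.23 × 0.77/128)} = Φ(1.30) = 0.90.

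**2. Timeline.** Doses are on days 7, 14, 28 and 42 (section 8.2.3). Surgery is 10 to 12 weeks after 5 weeks of chemoradiotherapy: weeks 15 to 17, days 105 to 119 (section 8.3, Table 4). Planned EOS is week 20, day 140. Dating the stop from the last dose:

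| Last dose | EOS at +28 days | 100-day window ends | Window end relative to surgery on day 105 / 119 |
|---|---|---|---|
| day 7 | 35 | 107 | 2 days after / 12 days before |
| day 14 | 42 | 114 | 9 days after / 5 days before |
| day 28 | 56 | 128 | 23 / 9 days after |
| day 42 | 70 | 142 | 37 / 23 days after |

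The substitute EOS therefore precedes surgery by at least 105 − 70 = 35 days. A patient who stays in the study is seen 140 − 119 = 21 to 140 − 105 = 35 days after surgery.

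**3. Effect on the verdict.** P(unsafe) = P(X > border), with X binomial on the number observed. The border stays at its n=50 value and the true rate is 46% (twice 23%).

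| Unobserved (assumed) | Observed | Border 18 | Border 19 |
|---|---|---|---|
| 0 | 50 | 0.90 | 0.84 |
| 3 | 47 | 0.82 | 0.73 |
| 5 | 45 | 0.74 | 0.64 |
| 10 | 40 | 0.49 | 0.36 |

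This does not assume that stoppers fare worse. Suppose they do, with an assumed 60% complication rate and the arm still at 46% overall. With 5 stoppers the remaining rate is (23 − 3)/45 = 0.444, and P(unsafe) at border 18 is 0.67. With 10 it is (23 − 6)/40 = 0.425, giving 0.31.

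**4. Recomputed border.** By the Table 2 method the border is 17 for 45 patients and 15 for 40. At a true 46%, P(unsafe) is then 0.83 and 0.82, so most of the loss from random gaps is recovered. Loss related to the outcome is not: with 10 stoppers at an assumed 60% or 70%, P(unsafe) is 0.68 or 0.56 even with the border at 15. Follow-up has to be repaired as well as the border.

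**The case against.** A reader might infer that every patient who stops for toxicity is left out of the primary analysis. The protocol does not support that. Section 11.1 sets no minimum number of doses and does not name its set as the primary population. A stop required by the product information follows the protocol, so it is not a violation. Exclusion is clear only for a patient who stops before any nivolumab; after one or two nivolumab doses the wording is ambiguous. Sections 7.1.6 (replacement), 11.4.2 and 11.4.4 all point towards counting these patients.

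A reader might also infer that their postoperative events are never seen. Section 9.6 says otherwise. Its window reaches past all planned surgery dates for a stop after day 28, and part of the range for earlier stops. Prolonged hospitalisation is a serious event, so many serious complications would be reportable, and later events thought related to drug or a protocol procedure are also requested. What stands is a contradiction between 7.1.6, 8.2.6 and 10.1 on one side and 9.6 on the other, not certain loss of data.

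Different populations for the descriptive toxicity tables and the complication comparison need not conflict in themselves. But the tables in 11.4.4 carry no decision rule, so they do not repair the primary count.

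Finally, the gap need not reverse a verdict when the excess is modest. If 8 of 50 stop with an assumed 50% complication rate and the rest have 23%, the arm rate is (4 + 9.66)/50 = 27.3%. The count then exceeds 18 with probability only 0.06 even with all 50 observed. The damage lies at large excesses, including the doubling the protocol names.

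**Conclusion.** The point holds as an unresolved contradiction with a one-sided consequence. Read through sections 7.1.6, 8.2.6 and 10.1, patients withdrawn for toxicity leave study follow-up at least 35 days before surgery. Read through section 9.6, some of their postoperative events would still be reported. The protocol does not say which governs, nor which of its populations the primary count uses. Because the border is fixed for 50, any outcome not observed moves the verdict towards safe.

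For a true doubling to 46% at border 18, the chance of declaring the treatment unsafe falls from 0.90 to 0.82, 0.74 or 0.49 with 3, 5 or 10 patients unobserved. These figures assume that the stated numbers go unobserved and, in the main table, that they are lost independently of outcome. The protocol gives no stopping rate, so they show a range and are not a forecast.

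**What to change.** 1. In sections 11.1 and 11.4.2, name one primary safety set, analysed by randomised arm: all treatment-arm patients with at least one dose of study drug, and all control-arm patients who started chemoradiotherapy. Completion of the sequence and protocol deviations should not affect membership. Keep the present sets as a sensitivity analysis. Treatment-arm patients who never received study drug should stay outside the main comparison, since they would dilute the rate.
2. Reconcile sections 7.1.6, 8.2.6 and 10.1 with section 9.6 so that leaving study drug is distinct from leaving the study. Unless consent is withdrawn, take surgical outcomes from routine care through the postoperative EOS, and make the 28-day visit additional.
3. Compute the Table 2 and Table 3 borders for the patients actually operated on and evaluated (Table 3 now counts recruited patients). Report those who did not reach surgery separately.

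The cost is a protocol amendment, some extra data entry for a few patients already in surgical care, and a count that may look slightly less favourable. No change is proposed to when or why a drug is stopped.
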